### Expected risks

2.3

The intervention proposed here generates minimal risks, as it involves noninvasive measurements. The informatics classes, as well as game practicing, will be done in the usual classroom. If the participant feels any discomfort, the proposed tasks must be stopped and the participant will be aided by the responsible professionals. Data will be collected in a private room, in the same place the participants have the informatics classes, attended only by the researchers and professionals skilled to help during its execution.

Although the procedure is noninvasive and the risks are minimal, the possible risks to physical or mental health are: eye strain due to sustained computer use, imbalance or pain during the movements imposed by the virtual games, or feeling sick or tired. Some embarrassment for not being able to or not understanding how to play the games may also happen. In any of these cases, the participant may withdraw from participation.

### Expected benefits

2.4

It is expected that repeated use of VR games will influence the motivation of the participants to use computers and allow them opportunities to acquire or develop motor abilities needed for it in an enjoyable way and, consequently, loneliness will be reduced.

Participation in the research will also contribute to identify how practicing different virtual games can influence performance of computer tasks and achieving the goal of every game. This may allow health and education professionals to adjust their practices in accordance to the characteristic of their attended population. If the addition of games with VR in the computer classes has positive results, they may be introduced as a standard practice in computer classes, for example.

### Intervention

2.5

There are 6 groups of computer classes for beginners offered by CRI, with a maximum of 10 students each. The classes last 2 hours, twice a week and include basic computer operations, the use of Word programs and introduction to the Internet.

For the intervention, the 6 classes of computer lessons for beginners will be randomly assigned into 2 groups, group 1 (G1) and group 2 (G2), with the same number of classes for each group.

The intervention will be divided into 2 phases, as shown in Fig. 1. In phase 1, G1 will have 8 conventional computer classes, while G2 will have 8 computer classes which will include 15 minutes of practicing games in a VR environment, using a physical interface (keyboard or mouse). In phase 2, intervention will be crossed between the groups. Therefore, G2 will have 8 conventional computer classes, while G1 will have 8 computer classes which will include 15 minutes of computer game practice. The games used for intervention (Labyrinth, Fitts, Motor Skill Analyzer [MOSKA], and Timing Coincident) will be described in the section Games for training.

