### Study population

2.1

It will be a convenience sample. The participants will be students in beginning level computer classes for seniors in the CRI in Ribeirão Pires, Sao Paulo, Brazil.

Because no study was found using the short version of the Social and Emotional Loneliness Scale for Adults (SELSA-S) before and after any intervention, sample calculation was not possible. However, there will be a minimum of 23 participants in this study, based on the largest sample that used VR in older adults found in the literature.^[13]^

The CRI Ribeirão Pires offers cultural, sportive, and intellectual activities for people over 50 years old, as used in the multicenter Studies on Global Ageing and Adult Health project of the WHO.^[19]^

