### Data analysis

8.3

Excel and SPSS version 2.1 for Windows will be used for data preparation and analysis. The significance level will be *P* ≤ 0.05.

The data will be presented as means and standard deviations and in frequency tables. Before the data analysis, the normality of all variables will be evaluated for skewness and kurtosis. To compare participants’ mood and loneliness, paired *t* tests, Kruskal–Wallis tests, Mann–Whitney *U* tests, or Pearson correlation coefficients will be used. The analysis will be blinded and will compare the 3 moments of data collection and the 2 groups (G1 and G2). To guard against the possibility of type 1 errors from making too many post hoc comparisons, we will carry out only those comparisons that have been planned based on our hypotheses.

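### Six intact classes are randomised, but section 8.3 names only tests that treat students as independent; if classmates' scores are correlated, the G1 v G2 test exceeds its 0.05 level

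*Protocol article*

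**What the plan says.** Section 2.5 (Intervention) describes six beginners' classes, "with a maximum of 10 students each", meeting for two hours twice a week. It states that "the 6 classes of computer lessons for beginners will be randomly assigned into 2 groups", "with the same number of classes for each group". Three classes thus form G1 and three form G2, and the two groups swap conditions after phase 1.

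Section 8.3 (Data analysis) lists paired t tests, Kruskal-Wallis tests, Mann-Whitney U tests and Pearson correlations for mood and loneliness. It adds that the analysis "will compare the 3 moments of data collection and the 2 groups (G1 and G2"). The threshold is given as "The significance level will be *P* ≤ 0.05". No class effect, cluster adjustment, mixed model or ICC is mentioned in this section or elsewhere.

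Section 2.1 (Study population) says that a "sample calculation was not possible" and that "there will be a minimum of 23 participants in this study". That number is taken from the largest earlier VR sample in older adults, and it counts students.

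**The concern.** When whole classes are allocated, the comparison of G1 with G2 can be no more certain than the variation between classes permits. Each test named in section 8.3 instead measures uncertainty from the spread between individual students, as if up to 60 people had been allocated one by one.

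The primary outcome makes correlation within classes plausible. Loneliness is a social outcome, and classmates spend four hours a week together. A friendship group forming in one class, or a disruption in another, would move several students' scores at once.

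At stake is whether such a class-level event could be reported as an effect of VR games. Section 2.4 (Expected benefits) foresees that positive results might make the games standard practice in computer classes.

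**Working it through.** **Inputs from the document.** 6 classes, 3 v 3, and at most 10 students per class (section 2.5). Minimum of 23 students (section 2.1), so 23/6 = 3.83 per class, taken as 4 below. Threshold 0.05 (section 8.3), treated as two-sided because sidedness is not stated.

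**Assumed inputs.** ICC of 0.02, 0.05 or 0.10, equal class sizes, normal data, total variance 1. The document gives none of these. The figure of 23 is a precedent, so there is no calculation to reproduce.

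**Step 1. True against assumed variance.** With m students per class:
- The variance of the group difference is larger than under independence by the design effect, DE = 1 + (m − 1) × ICC.
- The pooled within-group variance that the test uses is on average slightly too small: s² = 1 − ICC × (m − 1)/(3m − 1).
- The test statistic is therefore too large by about √(DE/s²). Dividing the nominal critical value by this factor gives the approximate true rejection rate, read from the t distribution with 6m − 2 df.

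Worked example, m = 10, ICC 0.05: DE = 1 + 9 × 0.05 = 1.45; s² = 1 − 0.05 × 9/29 = 0.9845; √(1.45/0.9845) = 1.214. The critical value with 58 df is 2.002, and 2.002/1.214 = 1.649. The two-sided tail area beyond 1.649 is 10.4%.

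| m | ICC | DE | s² | effective cut-off | type I error by formula | simulated t test |
|---|---|---|---|---|---|---|
| 4 | 0.02 | 1.06 | 0.995 | 2.009 | 5.7% | 5.7% |
| 4 | 0.05 | 1.15 | 0.986 | 1.921 | 6.8% | 6.8% |
| 4 | 0.10 | 1.30 | 0.973 | 1.794 | 8.7% | 8.8% |
| 10 | 0.02 | 1.18 | 0.994 | 1.837 | 7.1% | 7.0% |
| 10 | 0.05 | 1.45 | 0.985 | 1.649 | 10.4% | 10.7% |
| 10 | 0.10 | 1.90 | 0.969 | 1.429 | 15.8% | 15.8% |

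The independent-samples t test is not itself on the list in section 8.3. The Mann-Whitney test is, and it behaves much the same: 5.1%, 6.1% and 7.6% with 4 per class, and 9.9% and 14.9% with 10 per class at ICC 0.05 and 0.10. A t test on class means (4 df) stayed at about 5% throughout.

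**Step 2. The cross-over contrast.** The treatment effect is estimated by comparing T2 − T1 between G1 and G2. A class effect that is the same at T1 and T2 drops out of each student's difference. Class-by-period variation does not. If it makes up a share ρ of the variance of T2 − T1, the formulas in step 1 apply with ρ in place of ICC. Simulated type I error of the individual-level t test on these differences was about 7% and 8-9% with 4 per class, and about 10.6% and 16% with 10 per class, at ρ = 0.05 and 0.10. The t test on class-mean differences held about 5%.

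**Step 3. Information in a class-level analysis.** Six classes in two groups leave 6 − 2 = 4 df, with a critical t of 2.78 against 2.08 on 21 df for 23 students. A permutation test on classes has C(6,3) = 20 allocations, so its smallest two-sided P is 2/20 = 0.10, which can never meet the stated threshold.

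**The case against.** **The size rests on an assumption.** This stands. No ICC is given. At ICC 0.01 with 23 students, the t test is at 5.2% and Mann-Whitney at 4.5%, which is no practical problem. Double-digit error needs nearly full classes as well as an ICC of about 0.05 or more. Nor does the article say who teaches. Sections 2.3 and 2.6 refer to the usual classroom, which may serve all six classes, and a room or teacher common to all of them would create no difference between classes. The case for correlation rests on shared company, not on teacher or room.

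**The cross-over deals with it.** Partly. It removes stable class differences but not class-specific change between phases.

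**Detail could sit in an analysis plan that is not shown.** Section 8.3 is a condensed list joined by "or", and its sentence on moments and groups names no test. Still, the article does not merely leave the method open. It names a family of tests, and none of them fits the randomisation it describes.

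**Stronger readings.** A reader might infer that every P value from section 8.3 will be too small. That does not follow. Kruskal-Wallis across the three repeated moments ignores the pairing within persons, which pushes P upwards: with 23 students, a within-person correlation of 0.5 and no class effect, its simulated type I error was 0.002. That is a separate fault. A reader might also infer that the minimum of 23 overstates the trial's power. Section 2.1 claims no power or precision, so there is nothing of that kind to refute. What can be said is that 23 counts students, while the randomised comparison has 6 units.

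**Conclusion.** The mismatch holds on the text alone: classes are randomised, and students are analysed as independent. That the G1 v G2 comparison exceeds 0.05 is conditional on a positive correlation of scores, or of changes, within classes. That is plausible for loneliness but not quantified in the document. At ICCs of 0.02, 0.05 and 0.10, the error is slight to modest near the stated minimum (about 5-6%, 6-7%, 8-9%) and material with full classes (about 7%, 10%, 15-16%). For the cross-over contrast, the relevant quantity is class-by-period variation; at 5% or 10% of the change variance, the inflation is similar. The conclusion covers the group and cross-over comparisons. It does not extend to Kruskal-Wallis across the three moments or to any claim about power.

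**What to change.** In section 8.3, name an analysis by the randomised unit. Either of these would do:

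- A t test on class-level contrasts, 3 v 3 with 4 df. For the phase 1 comparison, use T0-adjusted class means at T1, with the adjustment made on students' scores before averaging. For the cross-over, use class-mean differences T2 − T1.
- A mixed model with random effects for class, class-by-period and participant, and a small-sample df correction such as Satterthwaite.

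The class-by-period term is essential. With balanced T1 and T2 data, a model with only class and participant intercepts gave the same treatment t, to about four decimals, as the individual-level t test on T2 − T1 (for example −2.9532 from both). It therefore leaves the inflation in place, and a df correction cannot supply a missing variance component.

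A class permutation test should not be the decision rule, given its floor of 0.10.

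In section 2.1, add that the randomised comparison rests on 6 classes. If a detectable difference is added, derive it for the cross-over contrast at class level, since a single-time parallel-group figure would describe a different design.

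The change is to analysis wording only, with no effect on recruitment, classes or data collection. The cost is wider confidence intervals and a test with only 4 df.

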**Figure 1 F1:**
[figure not shown]
Study flow.

### Data collection

2.6

Data collection will be in the usual computer classroom and done by the researchers and expert professionals available to help during its execution. The participants will be seated comfortably in an adjustable chair, or in their own wheelchair, whichever is the case. In order to protect confidentiality during and after the trial, the participants will be assigned numbers during data collection and their names would not be used during data analysis.

Data collection will be done at 3 times: moment 0 (T0) – before the beginning of the computer classes; moment 1 (T1) – after Phase 1; and moment 2 (T2) – after phase 2. The study flow is on Fig. 1.

In the first meeting (T0), the informed consent (IC) form will be presented and explained. After signing the IC, a characterization questionnaire, the SELSA-S,^[22]^ the Mini Mental,^[23]^ and the Brunel Mood Scale^[24]^ will be filled in, always with help of one of the researchers. Then, instructions for playing the VR games will be given verbally by the researcher. Participants will then play 3 games about which data will be collected: Random, MoviLetrando, and Reaction Time. The time for data collection will be up to 40 minutes.

During T1 and T2, the procedure will be the same as in T0, except for the IC explanation and Mini-mental testing.

### Instruments

2.7

Instruments for assessment

A characterization questionnaire with information on gender, age, education, marital status, and use of computer and mobile phone will be used to characterize and homogenize the sample. Scores on the Mini-Mental Status Exam,^[20,21]^ which quickly screens and evaluates cognitive function, will be used as an exclusion criterion.

Evaluating the mood of participants may aid in evaluating their performance during the games. This hypothesis is based on findings of a negative correlation between mood and the sensory and motor functioning of subjects, suggesting that low mood might interfere with functional balance.^[25]^ Therefore, the Brunel Mood Scale was administered.

To evaluate loneliness, the Portuguese version of the short Social and Emotional Loneliness Scale for Adults, SELSA-S,^[22]^ validated for the elderly population, was used.

The questionnaires will be, preferably, filled out in an electronic format developed through Epi Info, which allows building questionnaires in a quick way and was developed by the Center of Diseases Control.^[26]^ Filling the forms directly on the computer allows defining answers that are mandatory, avoiding questions without answers. The answers will be exported to Microsoft Excel, avoiding typos.

The games used in the study, Random, MoviLetrando, and Reaction Time, will be used to assess performance through reaction time, hits, and misses.

## Random

3

The task in Random consists of a screen that presents a set of 126 3D bubbles (Fig. 2A) arranged in rows and columns. The goal is to reach, with the mouse cursor, the bubble that changes color (from gray to red) randomly. In this case, the target is a virtual object and the interaction device to hit the target is the mouse. The game saves information on performance such as score of the targets hit and time.

**Figure 2 F2:**
[figure not shown]
Games for assessment. (A) Random; (B) MoviLetrando; and (C) Reaction Time.

## Moviletrando

4

The game MoviLetrando^[27]^ was developed by a multidisciplinary development team at the Laboratory for Research on Visual Applications, Santa Catarina State University (LARVA-UDESC). MoviLetrando uses the concept of Projection VR, a game with movement and without an interaction device to facilitate usability.

To play MoviLetrando, a webcam and a conventional laptop are necessary. The image captured by the camera is the player himself/herself and the game scenario (Fig. 2B), helping to develop proprioception.

A reference letter or number and is generated in the upper part of the picture and, at the same time, there is a sound representing this reference symbol. A set of symbols is shown below, one of which is equal to the reference. The player's goal is to use the movement of their arms and hands to “touch virtually” the correct symbol. Between the reference symbol and the set of symbols arranged in the scene, there is a bar representing the exposure time of symbols, that is, the time that the player has to capture a symbol.

The score in MoviLetrando is given through the symbols’ arrangement and exposure time. The game works according to the concept of levels that evolve according to the player's performance. The symbols are formed with numbers, vowels, consonants, and numerical sets, which can be set individually or in combination. In addition, one can set the symbol size to be presented. For this experiment, we opted for the level that uses numbers from 1 to 10.

The player must put together strategies to achieve the correct symbol and can do this with any part of the body, usually making use of the hands.

At the end of each game, information about performance, such as hits, errors, and score are saved. It is also possible to register several people in the database. With all these data, it is possible to make an analysis of the evolution of each participant's performance during a given period of playing the game.

## Reaction time

5

Reaction Time is a game which the participant must look to a white computer screen with a white square. Suddenly, the square turns yellow and, when that happens, the participant must press the space bar so the square turns white again. It is repeated for 14 times. The program calculates how long the participant takes to react after the square turns yellow (Fig. 2C).

## Games for training

6

### Labyrinth

6.1

The Labyrinth game used for training in this study was developed by the Department of Mathematics at the Federal University of Rio Grande do Sul.^[28]^ The task consists of negotiating a labyrinth with only one correct path to the exit, using the 4 arrows on keyboard. It produces a realistic labyrinth escape scenario; and therefore, the player is allowed to see only the part of the labyrinth he is in. However, to make the game easier, it is possible to opt to view the entire labyrinth during the game. The exit is indicated by an “X” (Fig. 3A). It is also possible to configure the size of the labyrinth. For this study an intermediate size of 9 × 9 was chosen.

**Figure 3 F3:**
[figure not shown]
Games for training. (A) Labyrinth; (B) Fitts; (C) Motor Skill Analyzer (MOSKA); and (D) Coincident Timing.

### Fitts

6.2

The 2nd training game was the “Fitts Reciprocal Aiming Task v.1.0 (Horizontal),” available in the public domain (http://okazaki.webs.com – available on the internet 25/04/2016) developed by Victor Hugo Alves Okazaki.^[29]^ This software represents the task proposed by Fitts law in a virtual environment (computer). For this research, the task is to use the mouse cursor of the computer to click on 2 bars, which are arranged vertically in parallel (Fig. 3B), intermittently, with the greatest possible speed and accuracy for a period of 10 seconds.

The task in this game has 3 difficulty index (DI) values. Each successive DI level is harder than preceding one, with larger spaces between the bars and/or a decrease in the size of the bar. However, due to the design of the program, only the default DI shown when the game is opened will be played during the training: that is the thinnest bar in the closer distance between them.

### Motor Skill Analyzer (MOSKA)

6.3

The software MOSKA, here used as a game, was developed to help the diagnosis and follow-up of problems in fine motor control of the upper limbs.^[30]^

The task allows the participant to draw a straight line by clicking with the mouse on a starting point (indicated by a red circle) and moving the mouse through the line to the end point (also indicated by a red circle) (Fig. 3C). Afterwards, the software calculates the errors, distance covered, and time in milliseconds.

The drawing of the line can be defined through x and y coordinates for the start and end points. This way, the game can be set up to require the drawing of horizontal, vertical, or diagonal lines.

### Coincident timing

6.4

Coincident timing, or coincidence of time and anticipation, refers to the cognitive ability to time the movement of a virtual object so as to arrive at a target coincident with the arrival of an object moving toward the same target.^[31]^ It is a widely used task in the motor learning area to assess the participant's cognitive development and maturation of visual and motor structures.^[32]^

It was decided to use the game software that consists of a task of virtual “coincidental timing.” The participant can receive immediate feedback of a hit or task error via different sounds, previously demonstrated to him. That game will be played during the intervention phase, using an interface with physical contact. In this case, the subject is represented as a virtual object that can be moved toward the target and is controlled via the keyboard (Fig. 3D).

The game “Coincident Timing” shows the sequence and firing speed of the cubes and records the total time of task execution (time spent to touch the sensor), as well as the time discrepancy between the arrival of the stimulus object and when the subject's virtual object arrived at the target.

## Material

7

Evaluation games will be played on laptops with Intel Core i7-4810MQ CPU 2.80 GHz processors and 8 Gb of RAM, with Windows 8 Professional de 64 bits operating systems.

For training games, the same desktop computers that are already used by the institution for computer classes will be used.

## Measures

8

All the data will be recorded at baseline, after 8 computer classes and after the other 8 computer classes which will include the practice of the games.

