**Methods and Analysis::**

This study will be a prospective longitudinal study with a randomised cross-over design, with subjects aged 50 years and older, of both genders, spontaneously enrolled in computer classes for beginners. Data collection will be done in 3 moments: moment 0 (T0) – at baseline; moment 1 (T1) – after 8 typical computer classes; and moment 2 (T2) – after 8 computer classes which include 15 minutes for practicing games in VR environment. A characterization questionnaire, the short version of the Short Social and Emotional Loneliness Scale for Adults (SELSA-S) and 3 games with VR (Random, MoviLetrando, and Reaction Time) will be used. For the intervention phase 4 other games will be used: Coincident Timing, Motor Skill Analyser, Labyrinth, and Fitts. The statistical analysis will compare the evolution in loneliness perception, performance, and reaction time during the practice of the games between the 3 moments of data collection. Performance and reaction time during the practice of the games will also be correlated to the loneliness perception.

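### The abstract and section 8 give every participant the order conventional then VR, which contradicts the cross-over and is reversed for G2, and section 8.3 does not say that the VR effect is the group-by-moment contrast

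*Protocol article*

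**What the plan says.** The protocol article describes the timing of the assessments in four places, and they do not agree.

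- **Abstract, Methods and Analysis:** the first follow-up is given as "moment 1 (T1) – after 8 typical computer classes", whereas the label for the second one reads "moment 2 (T2) – after 8 computer classes which include 15 minutes for practicing games in VR environment". Neither label is limited to a group. The analysis sentence that follows compares loneliness across the three moments and does not mention group.
- **Section 8, Measures:** all data are recorded at baseline, "after 8 computer classes and after the other 8 computer classes which will include the practice of the games". The games are attached to the second block of classes, again for everyone.
- **Section 2.5, Intervention:** "In phase 1, G1 will have 8 conventional computer classes, while G2 will have 8 computer classes which will include 15 minutes of practicing games". The interventions are then crossed, so in phase 2 G1 has the games and G2 has conventional classes.
- **Section 2.6, Data collection:** "moment 1 (T1) – after Phase 1; and moment 2 (T2) – after phase 2". This wording names no condition and is right for both groups.

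Section 8.3, Data analysis, lists paired and two-sample tests and a correlation as alternatives. It says that the analysis "will compare the 3 moments of data collection and the 2 groups (G1 and G2". It does not say how group enters the comparison of moments.

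**The concern.** The abstract and section 8 describe a single-sequence before-after study, whereas sections 2.5 and 2.6 describe a randomised cross-over. An analyst who took the condition from the abstract would give the wrong one to both post-baseline assessments of every G2 participant.

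The wording also affects the primary outcome analysis. Under the abstract's labels, T2 against T1 looks like VR against conventional classes. In the cross-over, that comparison taken over all participants adds the VR effect in one direction for G1 and in the other for G2. It also keeps the whole change from phase 1 to phase 2. On the document's own account such a change is plausible: section 2.5 says that the classes introduce the Internet, and the Introduction cites a trend to less loneliness in older adults who learned to use it. A fall in loneliness caused by the classes could be credited to the games, or a real effect of the games could be missed.

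**Working it through.** The plan states no figure to reproduce. The minimum of 23 participants in section 2.1 was not calculated from an effect size. The check is therefore algebraic, with a simulation under assumed inputs.

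**Inputs from the document.** There are two sequences with three classes each and at most 10 students per class (section 2.5). The minimum is 23 participants (section 2.1), and the level is 0.05 (section 8.3). The number of participants per group is not fixed.

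**Assumed.** τ is the effect of VR on the loneliness score, p the change from T1 to T2 common to both groups, and c the share of τ that G2 still holds at T2 (0 = transient, 1 = fully persistent).

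**Expected values, apart from a common starting level:**

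| | T1 | T2 | T2−T1 |
|---|---|---|---|
| G1 | 0 | τ + p | τ + p |
| G2 | τ | cτ + p | (c−1)τ + p |

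**Moments compared, pooled over groups.** The mean of T2−T1 is τ[n1 + n2(c−1)]/(n1+n2) + p. With n1 = n2 this is cτ/2 + p.

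| Split G1/G2 | Share of τ, c = 0 | Share of τ, c = 1 |
|---|---|---|
| equal | 0% | 50% |
| 12/11 | 1/23 = 4% | 12/23 = 52% |
| 15/8 | 7/23 = 30% | 15/23 = 65% |
| 8/15 | −7/23 = −30% | 8/23 = 35% |

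In every row 100% of p is added. At 8/15 with c = 0 the sign is reversed.

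**Groups compared, pooled over T1 and T2.** G1 averages (τ + p)/2 and G2 averages (τ + cτ + p)/2. The difference G1−G2 is −cτ/2, which is zero when c = 0. A pooled test of moments together with a pooled test of groups would thus fit the wording of section 8.3, and neither would estimate τ.

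**Between-sequence contrast.** Half the G1-minus-G2 difference in T2−T1 is [τ − (c−1)τ]/2 = τ(1 − c/2). The period change drops out. The result is τ when c = 0, 0.75τ when c = 0.5 and 0.50τ when c = 1.

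**G1 versus G2 at T1.** The difference G2−G1 is τ for any c, because phase 2 has not yet happened.

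**Simulated power.** There were 20,000 runs per setting, with a 12/11 split, an SD of 1 for the within-person T2−T1 difference, p = 0 and two-sided 0.05:

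| τ (SD units) | c | By sequence | Pooled T2−T1 |
|---|---|---|---|
| 0.5 | 0 | 63% | 3% |
| 0.8 | 0 | 96% | 1% |
| 0.5 | 1 | 21% | 20% |
| 0.8 | 1 | 45% | 43% |

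The simulation treats participants as independent although whole classes are randomised. The figures illustrate the gap between the analyses and do not forecast the trial's power.

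**The case against.** The strongest reply is that the operative text is right. Section 2.6 defines T1 and T2 correctly, section 2.5 says what each group receives, and group and moment together fix the condition of every assessment. Section 8 does not use the labels T1 and T2; only the abstract ties a condition to them. The Introduction states the comparison by condition, and section 8.3 names both groups. The exact model may stand in an analysis plan that is not shown.

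Much of this stands. A reader might infer that the trial will take pooled T2−T1 as the VR effect and so cancel most or all of it. The documents do not support that. No section says that T2−T1 will be read in this way, and section 8.3 compares G1 with G2 as well. The extent of any loss also depends on carryover and group sizes that the documents do not give: with full persistence about half of the effect remains, and the two analyses then have similar power.

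Two things remain. The contradiction is between positive statements, made in the abstract and again in section 8, so it is not a detail left to a fuller document. And section 8.3 can be met in full by tests that do not isolate the VR effect.

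**Conclusion.** The point holds as an internal contradiction with a consequence for the analysis. The abstract and section 8 fix an order that is true for G1, reversed for G2, and at odds with sections 2.5 and 2.6. The abstract's moment-only comparison, and section 8.3 as worded, leave the source of the VR estimate open.

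The size is conditional. If moments were pooled over equal groups, the comparison would carry between 0% (transient) and 50% (fully persistent) of the VR effect, plus all of the period change. Unequal groups shift this range; at 15/8 or 8/15 with no carryover the share is plus or minus 30%. Carryover, participants per group, effect size and SD are all assumptions. The between-sequence contrast removes the period change, but it equals the VR effect only without carryover. The matter should be settled before analysis, because section 8.3 limits testing to comparisons planned from the hypotheses.

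**What to change.** 1. In the abstract and section 8, define the moments as sections 2.5 and 2.6 do: T1 is the end of phase 1 (G1 conventional, G2 VR), and T2 is the end of phase 2 (G1 VR, G2 conventional).
2. In section 8.3, state that VR versus conventional classes is estimated by the between-sequence contrast, half the G1-minus-G2 difference in T2−T1. Call comparisons of moments alone descriptive.
3. Say there that this contrast equals the VR effect only if nothing carries over, and otherwise τ(1 − c/2). Report beside it the G1 versus G2 comparison at T1 adjusted for T0, which carryover does not affect.
4. Add to the dataset one variable giving the condition of the phase just completed.

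The cost is a few sentences and one derived variable. No new data, visits or participants are needed.
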